#### Quality control of the module contents

The modules for the intervention group were appraised for their contents and relevance by expert teams. For the immunisation health educational intervention modules, the team comprised of four public health specialists and a medical sociologist, a health educator, and a mid-wife. The intervention will be pre-tested with a sample of twenty pregnant women (35 gestational weeks) from the same hospital, who will not be part of the study. Appropriate feedback will then be obtained from the participants; this will include knowledge, attitude, outcome expectation, self-efficacy, cultural beliefs and assumptions of religious regulations components and appropriate modifications and corrections will be further effected.

### Data collection methods

The data collection tools that will be used comprised of a questionnaire and the study pro forma *(Refer to S5 and S6 Files).*

### Questionnaire

#### Questionnaire development

The study will use a guided questionnaire in collecting the necessary information. The questionnaire is first developed in English language. Its content validity has been assessed by an expert group [61], which involved six public health specialists and one medical sociologist who went through the questionnaire to ensure that the wordings of its items are clear, and that they represent their content domain [62]. The questionnaire was later translated into Hausa language via the process of translation and adaptation of instruments figured by the World Health Organization [63].

#### Questionnaire quality control

This will be entailed ensuring the validity and reliability of the questionnaire, as well as adequately training the enumerators. The questionnaire Content Validity Ratio (CVR) was carried-out while face validity and exploratory factor analysis will be performed before the commencement of the intervention.

#### Study pro forma

The researcher designed a study hand cards which will be used to collect information about childhood immunization uptake. The hand cards will be given immediately after recruitment, and will be submitted to the researcher at three months post-delivery after Penta 3 uptake. The card has participant’s serial number, basic bio-data, and a short appeal to the attending physician or nurse, informing them that the patient is enrolling into a follow-up study, and his/her help is needed to kindly fill the blanks provided on the card. The items it contained are: childhood immunization uptake and date given (BCG, Hep B-0 and OPV-0; OPV-1, PCV-1 and Penta-1; OPV-2, PCV-2 and Penta-2; OPV-3, PCV-3 and Penta-3).

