## Background

The immune system of children is stimulated by vaccines to fight against diseases or infections. It is a well-established fact that immunisation is a tool that can effectively control and eradicate life-threatening infectious diseases [1]. Immunisation is considered as one of the most successful and cost-effective public health sustainable interventions for human beings against diseases that affect our health [2]. Routine immunisation plays an important role in reduction of child mortality, resulting from vaccine preventable diseases (VPDs). WHO revealed that immunisation has been estimated to prevent 3 million deaths globally every year [3].

Despite the efforts made by health organizations to combat diseases, vaccine preventable diseases have remained the most common cause of childhood mortality, which is estimated at 3 million deaths around the world annually [4]. In Nigeria, VPDs accounted for 17% and 22% of under‐five childhood morbidity and mortality respectively [5].

In Nigeria, routine vaccination coverage for all recommended vaccines has remained poor. However, there was an increase in vaccination coverage from 25.4% of eligible children (12–23 months of age) in 2013 to 31% in 2018 [6]. In Zamfara State, only 7.4% of the children are fully immunized [6]. Table 1 shows the individual vaccine uptakes comparing Zamfara state with Nigeria. According to the Expand Program on Immunisation (EPI), every child in Africa must receive one dose of Bacillus Calmette Guerin (BCG), Oral Polio Vaccine (OPV0) and Hepatitis B Vaccine (HBV1) at birth, Penta1 & OPV1 at 6 weeks of age, Penta2 & OPV2 at 10 weeks of age, Penta3 & OPV3 at 14 weeks old and measles and yellow fever at 9 months old [6].

**Table 1 pone.0263436.t001:** Individual vaccine uptakes.

Vaccines	BCG	DPT1	DPT3	OPV3	Measles
Nigeria	66.7%	65.3%	50.1%	47.2%	54%
Zamfara State	16.1%	17.1%	10.8%	15.2%	12.2%

Nigeria Demographic and Health Survey 2018 [6]

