### Intervention

The participants in the intervention group will receive the ‘‘Immunisation Health Education Intervention” while the participants in the control group will receive ‘‘usual care”. The proposed interventions will be implemented at 35 gestational weeks after the baseline data has been collected from the participants. Based on the recommendation of McMillan [59], educational interventions should be carried out using approaches that are in accordance with what is used in practice. It is based on this, that the delivery of educational interventions in this study will be done at group levels in a two session. Every session will be composed of forty participants, while the facilitator of each of the sessions will be a midwife nurse.

The process of module delivery will be closely monitored and supervised by the investigator, and the relevant feed-back will be given to the facilitator in order to ensure that the module is followed accordingly. The five modules will be delivered by the facilitator, who will ensure that the participants are actively engaged. It is estimated that the delivery sessions will last for 30 minutes, 30 minutes, 30 minutes, 1 hour, 30 minutes, 45 minutes, 1 hour and 30 minutes. For modules 1, 2, 3, 4 and 5 respectively *(Refer to S2 File)*. The participants will be allowed to take short breaks of about 10 to 15 minutes between modules. Each participant will be given the chance to demonstrate what she has learnt, and corrective feed-back will be provided at the end of the modules. A compensation fees of (500 Naira) approximately 1.2 USD will be given to the participants in the intervention group in favour of their transportation. The mothers in the intervention group will also be receiving a mobile call reminder at 7 days and 1 day before their childhood immunisation schedule. The participants in the control group will not receive any mobile call reminder. Any mother in either the intervention or control group who completed her child vaccination from 0-doses to penta-3 will receive a baby pampers at the end of the intervention which will cost N700 (Naira) approximately 1.5 USD as recommended by Bandura’s [60].

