### Outcomes

The primary outcome for the proposed study is childhood immunisation uptake and the secondary outcomes are: improved knowledge scores, improved attitude scores, improved outcomes expectation scores, improved self-efficacy scores, improved cultural beliefs scores and improved assumptions of religious regulations scores. They will be taken at 6 weeks post-delivery, 10 weeks post-delivery and 14 weeks post-delivery *(Refer to S3 File).*

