In order to determine within-group differences with time for knowledge scores, attitude scores, outcome expectation scores, self-efficacy scores, cultural beliefs scores and assumptions of religious regulations scores the researcher will conduct one-way repeated measures analysis of variance (ANOVA) for these variables if there is no substantial non-normality of the residuals. Intention-to-treat analysis (ITT) will be carried-out separately for each group and replacement of missing data will be done through using multiple imputations technique. The estimated outputs that will be obtained after ITT analysis will then be pooled into a single data set, after that, the Generalized Linear Mixed Models (GLMM) analysis will be carried-out to investigate the overall effectiveness of the intervention using 95% Confidence Interval (CI) and 0.05 will be set as the level of significance. Two measures of effect size will be used in this study: Partial Eta squared and the coefficients of the fixed effects. Partial Eta squared will be used in the mixed design repeated measures ANOVA, and will be classified as small, medium or large effect (0.2, 0.5 and 0.8) respectively according to the magnitude. The coefficients of the fixed effects will be used in the GLMM analysis.

In order to check the robustness of the result, sensitivity analysis will be performed to determine the effect of drop out and non-response on the findings of the proposed study, the GLMM analysis will be repeated again without replacing the missing values. The differences between the coefficients obtained after replacement (intention to treat analysis) and before replacement of the missing values (per-protocol) will then be calculated and expressed as percentages of the former.

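### Return of the hand card is tied to Penta 3, with no stated route for non-completers, so the primary outcome may be missing according to its own value

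*Protocol article*

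**What the plan says.** Under Outcomes: "The primary outcome for the proposed study is childhood immunisation uptake", taken at 6, 10 and 14 weeks post-delivery. Study process also says that the follow-up at those three times is to assess uptake.

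Under Data collection methods: "The data collection tools that will be used comprised of a questionnaire and the study pro forma". Of these two, only the pro forma is described as recording doses. Study pro forma calls it "study hand cards which will be used to collect information about childhood immunization uptake". It holds "childhood immunization uptake and date given" for each block from birth to Penta 3. The card is given out at recruitment and "will be submitted to the researcher at three months post-delivery after Penta 3 uptake".

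Under Intervention, any mother in either arm "who completed her child vaccination from 0-doses to penta-3 will receive a baby pampers at the end of the intervention". Reminder calls go to the intervention arm only.

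Under Data analyses, the data come from the questionnaire and a child immunization record that is not defined. For gaps, "replacement of missing data will be done through using multiple imputations technique", separately in each group. The one sensitivity analysis repeats the mixed model without replacing missing values.

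The Background gives the schedule as "Penta3 & OPV3 at 14 weeks old".

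**The concern.** The sentence on card submission makes hand-in follow the event that the trial is meant to measure. A mother whose child has Penta 3 has a stated moment to return the card and a small reward for completing. A mother whose child does not has neither. Applied as written, whether the outcome is observed would depend on the outcome.

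Multiple imputation under missing-at-random, and an analysis of observed data only, both learn from the cards that came back. If those over-represent completers, both give uptake that is too high, and their agreement would look like robustness. If the imbalance in return also differs by arm, the treatment effect is distorted as well.

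The timing adds to the problem. Three months is about 13 weeks, Penta 3 is due at 14 weeks, and the last contact is at 14 weeks.

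**Working it through.** **No figure to reproduce.** The article states no card-return rate, missing-data rate or bias. The return rates below are assumptions, shown over a range.

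**Inputs from the article**
- 382 randomised equally, so 191 per arm (Study process).
- Illustrative true uptake: DPT3 33% v 20% (Sokoto trial) and 72.1% v 51.7% (Karachi trial), both from the Background.
- Timing: 3 × 365.25 / 12 / 7 = 13.04 weeks, against 14 weeks for Penta 3.

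**Formula.** Let p be true uptake, and let rc and rn be the return probabilities of completers and non-completers. Uptake among returned cards is

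q = p·rc / [p·rc + (1 − p)·rn].

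Imputation within arm under missing-at-random, with no informative earlier data, reproduces q in expectation.

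**Equal return in both arms, rc = 0.95** (differences from unrounded values)

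| rn | True 33% v 20% (13.0 points) | True 72.1% v 51.7% (20.4 points) |
|---|---|---|
| 0.95 | 33.0 v 20.0 (13.0) | 72.1 v 51.7 (20.4) |
| 0.75 | 38.4 v 24.1 (14.4) | 76.6 v 57.6 (19.0) |
| 0.50 | 48.3 v 32.2 (16.1) | 83.1 v 67.0 (16.0) |
| 0.25 | 65.2 v 48.7 (16.5) | 90.8 v 80.3 (10.5) |
| 0 | 100 v 100 (0) | 100 v 100 (0) |

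Uptake is overstated in every row where rn is below rc. The risk difference rises, falls or vanishes depending on the starting rates.

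**Odds ratio.** The odds of q are [p/(1 − p)]·(rc/rn). With rc the same in both arms,

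observed OR = true OR × rn(control) / rn(intervention).

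The true OR for 33% v 20% is (0.33 × 0.80)/(0.20 × 0.67) = 1.97. If rn is equal in the arms and above zero, the observed OR is also 1.97 (2.41 for the Karachi rates).

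**Unequal non-completer return, rc = 0.95**

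| rn intervention v control | OR when true OR is 1.97 | Difference, true 33% v 20% | OR when true OR is 1.00 | Difference, 20% in both arms |
|---|---|---|---|---|
| 0.65 v 0.60 | 1.82 | 13.5 points | 0.92 | −1.6 points |
| 0.80 v 0.70 | 1.72 | 11.6 | 0.88 | −2.4 |
| 0.80 v 0.60 | 1.48 | 8.5 | 0.75 | −5.5 |
| 0.60 v 0.40 | 1.31 | 6.6 | 0.67 | −8.9 |
| 0.40 v 0.60 | 2.96 | 25.6 | 1.50 | +8.9 |

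Worked case, 0.80 v 0.60: intervention 0.3135/(0.3135 + 0.536) = 36.9%; control 0.190/(0.190 + 0.480) = 28.4%; OR = 1.97 × 0.60/0.80 = 1.48.

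By normal approximation on the expected returned cards (two-sided 5%), that split leaves power of about one third, against about 82% with all 191 per arm observed. It rejects a true null at 20% about 18 to 19% of the time. With 0.65 v 0.60 the null rejection rate is about 6%.

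**The case against.** A reader might infer that the card is the only source of the outcome, that every non-completer is therefore missing and imputed, that earlier doses cannot inform the imputation, and that the arm comparison must be biased. The article does not support any of these as stated.

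- **Only source.** Uptake is said to be assessed at 6, 10 and 14 weeks, and Data analyses names a child immunization record. That record may be the card or something else. The supplementary files on outcomes and tools are not shown. What stands is that the card is the only instrument described as recording doses.
- **Non-completers missing.** The hand-in phrase can be read as the expected time of return for everyone. All participants have a 14-week contact, and a card with separate dated blanks for each block can show a partial series. Nothing says that incomplete cards are refused. Even so, the rule for non-completers remains unstated.
- **Earlier doses lost.** If uptake really is captured at 6 and 10 weeks, those doses could inform the imputation. The article does not say how they would be captured when the card comes in once.
- **Biased effect.** The planned effect measure is the fixed-effect coefficient of the mixed model. The link is not stated; with a logit link, equal outcome-dependent return leaves the odds ratio intact. Bias needs unequal return. The intervention-only calls are reminders before due doses, not outcome tracing, so unequal return is possible rather than shown, and its direction is unknown.

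How a missing card is counted may also be settled in an analysis plan that is not shown. The wording of the hand-in rule is in the article itself and does not depend on that plan.

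**Conclusion.** The point holds in conditional form and should be fixed. The article ties a single hand-in of the card to Penta 3, gives no route for non-completers, and leaves this unreconciled with its own assessment times, its undefined immunization record and the 14-week due date.

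If non-completers return cards less often, uptake is overstated in each arm, and neither planned analysis corrects it unless informative earlier-dose data enter the imputation. The risk difference can move either way. The odds ratio is distorted only if return among non-completers differs by arm (taking completer return as equal). The distortion ranges from slight (0.92 under the null at 65% v 60%) to material (0.75 at 80% v 60%), and it reverses if the gap reverses. These sizes rest on assumed return rates and show sensitivity; they do not predict this trial's bias.

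**What to change.** 1. Reword Study pro forma so that the card is collected or transcribed from every mother at the 6-, 10- and 14-week contacts and at one fixed closing date, whatever doses were given. This also removes the clash between three months and 14 weeks.
2. Verify all 382 serial numbers against the Federal Medical Centre Gusau immunisation record, and state that this is the record meant in Data analyses. Eligibility already requires an intention to immunise there.
3. Report card return by arm.
4. Add a sensitivity analysis that counts a child with no dose on card or record as not taken. It belongs there rather than as the primary rule, because it has its own bias if capture of records differs by arm.

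The cost is a few sentences and a record look-up for 382 children. Doses given elsewhere and not on a returned card may still be missed. Study process describes follow-up as still to come, so on the article's own account the change can be made in time.

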#### Data analyses

The data analyses will be conducted using IBM Statistical Package for Social Sciences (SPSS) version 25. The data that will be collected from questionnaire and the child immunization record will be entered into the software, followed by data cleaning.

Maternal age, knowledge scores, attitude scores, outcome expectation scores, self-efficacy scores, cultural beliefs scores and assumptions of religious regulations scores will be subjected to both statistical and graphical normality tests due to the fact that they are continuous variables.

Mean and standard deviation will be used as the measures of central tendency and dispersion to summarise continuous variables that are normally distributed while mean or median will be used to summarised skewed data. Categorical data will be summarised as frequency and percentage.

Chi-squared test will be carried-out to make a baseline comparison of the groups by their sociodemographic characteristics, obstetrics factors, healthcare system factors, responses on immunisation knowledge, attitude, outcome expectation, self-efficacy cultural beliefs and assumptions on religious regulations. Fisher’s Exact test will be conducted for variables where up to 20% of the cells have less than five observations. Independent t-test will be carryout to determine the between-group differences in the knowledge scores, attitude scores, outcome expectation scores, self-efficacy scores, cultural beliefs scores and assumptions of religious regulations scores at three time points.

In order to determine within-group differences with time for knowledge scores, attitude scores, outcome expectation scores, self-efficacy scores, cultural beliefs scores and assumptions of religious regulations scores the researcher will conduct one-way repeated measures analysis of variance (ANOVA) for these variables if there is no substantial non-normality of the residuals. Intention-to-treat analysis (ITT) will be carried-out separately for each group and replacement of missing data will be done through using multiple imputations technique. The estimated outputs that will be obtained after ITT analysis will then be pooled into a single data set, after that, the Generalized Linear Mixed Models (GLMM) analysis will be carried-out to investigate the overall effectiveness of the intervention using 95% Confidence Interval (CI) and 0.05 will be set as the level of significance. Two measures of effect size will be used in this study: Partial Eta squared and the coefficients of the fixed effects. Partial Eta squared will be used in the mixed design repeated measures ANOVA, and will be classified as small, medium or large effect (0.2, 0.5 and 0.8) respectively according to the magnitude. The coefficients of the fixed effects will be used in the GLMM analysis.

In order to check the robustness of the result, sensitivity analysis will be performed to determine the effect of drop out and non-response on the findings of the proposed study, the GLMM analysis will be repeated again without replacing the missing values. The differences between the coefficients obtained after replacement (intention to treat analysis) and before replacement of the missing values (per-protocol) will then be calculated and expressed as percentages of the former.

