### Specific objectives

The specific objectives of this study are:

To determine and compare the baseline of respondents between intervention and control group at baseline according to:
Parental socio-demographic characteristics (maternal age, maternal education, paternal education, maternal marital status, maternal occupation, area of residence, number of siblings, religion, ethnicity and family income).Obstetric history (antenatal care follow-up, Maternal Tetanus Toxoid (MTT) vaccine and preceding birth intervals).Knowledge scores on (immunization, knowledge on VPDs and knowledge on EPI schedule).Outcome expectation scores (benefit of immunization and seriousness of VPDs).Attitudes scores (maternal perceptions towards childhood immunization).Self-efficacy scores (vaccine safety and vaccine side effect).Environmental factors (assumptions of religious regulations scores, cultural belief scores, distance to health facility, mode of transportation, hospital accessibility and attitude of hospital staff).To develop and implement an immunization health educational intervention based on Social Cognitive Theory for pregnant women in Federal Medical Centre Gusau, Zamfara State, Nigeria.To compare the total immunization knowledge, attitude, outcome expectation, self-efficacy, cultural beliefs and assumptions of religious regulations scores within the intervention and control group at baseline to 6-weeks post-delivery, 10-weeks post-delivery and 14-weeks post-delivery.To compare the knowledge, attitude, outcome expectation, self-efficacy, cultural beliefs and assumptions of religious regulations scores between the intervention and control group at baseline to 6-weeks post-delivery, 10-weeks post-delivery and 14-weeks post-delivery.To determine the effects of the intervention on improving child immunization uptake in Federal Medical Centre Gusau, Zamfara State, Nigeria.

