### Sample size determination

The minimum sample size required to test the proposed study hypotheses has been determined using the formula for comparing two proportions in selected samples of both intervention and control groups [57]. This formula gave the required number (n) for each group. This provided a total sample size of 196 participants in each group, which will then be multiplied by two since the study is comprised of two arms. Therefore, 392 are the calculated sample size required to test the hypothesis for this study *(Refer to S1 File).*

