### Study process

An illustration of the study process was done in accordance with CONSORT statement [55]. During the eight weeks recruitment period, a total of 551 pregnant women had been assessed for possible inclusion in the study out of which 159 did not meet the inclusion criteria while ten declined to participate. The remaining three hundred and eighty-two participants were then randomly assigned equally, to either the intervention or the control group. SPIRIT schedule of the study and flow diagram of the study are shown in Figs 1 and 2 respectively. The baseline data of the study participants has been taken and they will both be followed up at 6 weeks post-delivery, 10 weeks post-delivery and 14 weeks post-delivery to assess the effect of the intervention regarding their knowledge, attitude, outcome expectations, self-efficacy, cultural beliefs and assumptions of religious regulations towards child immunization, as well as to assess their child immunization uptake.

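### As worded, the trigger for Fisher's exact test runs the wrong way and counts observations rather than expected counts, so sparse 2x2 baseline tables go to chi-squared, which for some of them overstates imbalance

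*Protocol article*

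**What the plan says.** In the protocol article, the Data analyses section sets the default: "Chi-squared test will be carried-out to make a baseline comparison of the groups by their sociodemographic characteristics". The list continues with obstetric and health-system factors and the responses to the questionnaire. The exception follows at once. Fisher's exact test "will be conducted for variables where up to 20% of the cells have less than five observations".

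These comparisons serve the first item under Specific objectives: "To determine and compare the baseline of respondents between intervention and control group at baseline". The variables named there include marital status, religion and ethnicity.

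The rule is not restated or corrected anywhere else in the article.

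**The concern.** The sentence has two separate defects.

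- **Direction.** The usual criterion accepts the chi-squared approximation while no more than 20% of cells are small, and turns to the exact test beyond that. Here the exact test is assigned at or below 20%, which leaves chi-squared for the sparser tables.
- **Type of count.** The criterion concerns expected counts, because these govern the quality of the approximation. The article counts observations ("cells have less than five observations").

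At stake is whether some baseline p-values are too small. A falsely significant difference between the arms could lead a reader to doubt a sound randomisation.

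**Working it through.** **Inputs**
- Women per arm: 191. Study process reports 382 randomised equally ("The remaining three hundred and eighty-two participants were then randomly assigned equally, to either the intervention or the control group"), and 382 / 2 = 191. The planned figure in Sample size determination is 196 per arm.
- Level: 5%. The article says "0.05 will be set as the level of significance", but for the GLMM. Its use for the baseline tests is my assumption.
- Continuity correction: not specified, so both versions are shown.

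The article gives no figure of its own to reproduce on this point.

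**Step 1: where the rule sends a 2x2 table.** The share of small cells can only be 0, 25, 50, 75 or 100%. One small cell already exceeds 20%, so the literal rule keeps chi-squared. A table with no small cell (0%) goes to Fisher. If at most 9 women in total have a characteristic, one arm must have 4 or fewer, so every such table goes to chi-squared.

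**Step 2: the test statistics.** Let a and b be the numbers with the characteristic in each arm, and m = a + b. With 191 per arm:
- uncorrected: X² = 382 (a − b)² / [m (382 − m)]
- continuity-corrected: X² = 382 (|a − b| − 1)² / [m (382 − m)]
- 5% critical value: 3.84

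| Split | Uncorrected X² | p | Corrected X² | Fisher p |
|---|---|---|---|---|
| 4 v 0 | 382 × 16 / (4 × 378) = 4.04 | 0.044 | 382 × 9 / 1512 = 2.27 | 0.123 |
| 5 v 0 | 382 × 25 / (5 × 377) = 5.07 | 0.024 | 382 × 16 / 1885 = 3.24 | 0.061 |
| 7 v 1 | 382 × 36 / (8 × 374) = 4.60 | 0.032 | 382 × 25 / 2992 = 3.19 | 0.067 |

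**Step 3: true error rate.** Under random allocation with m fixed, P(a) = C(191, a) C(191, m − a) / C(382, m). For m = 4 the uncorrected test rejects only at 4 v 0 and 0 v 4:

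2 × (191 × 190 × 189 × 188) / (382 × 381 × 380 × 379) = 0.123.

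For m = 5 it rejects only at 5 v 0 and 0 v 5: 0.1230 × 187 / 378 = 0.061. All sparse totals:

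| Total m | Uncorrected chi-squared | Fisher, and corrected chi-squared |
|---|---|---|
| 1 to 3 | 0.0% | 0.0% |
| 4 | 12.3% | 0.0% |
| 5 | 6.1% | 0.0% |
| 6 | 3.0% | 3.0% |
| 7 | 1.5% | 1.5% |
| 8 | 6.7% | 0.7% |
| 9 | 3.7% | 3.7% |

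(For m = 1 the only possible split gives X² = 382 / 381 = 1.00, so it never rejects.) With 196 per arm the results agree to within 0.1 percentage point.

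**Step 4: larger tables.** Seven assumed sparse tables with 3 to 5 categories were simulated, with 40,000 random allocations each and 191 per arm. Chi-squared rejected in 0% to 4.4% of draws, so it was not inflated.

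**Step 5: under the usual rule.** For m = 9 or less, the expected count per arm is at most 4.5. Two of the four cells (50%) are then below five, and the table goes to Fisher. The rates at m = 4, 5 and 8 fall to 0.0%, 0.0% and 0.7%.

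**The case against.** **The wording may be a language slip.** Read literally, the rule also sends every table with no small cell to Fisher, so the stated default would apply only to sparse tables. The authors may have meant as much as 20% or more, and the English is loose elsewhere. This is a fair reading and may well be the intended one. It does not rescue the sentence: the observed-count criterion stays wrong, and a pre-specified rule should not have to be read against its literal meaning.

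**The error rate is selective.** This stands. Of the totals 1 to 9, only 4, 5 and 8 exceed 5%, and 12.3% is the worst of them. A continuity correction removes the excess.

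**The rule does not always pick an unsuitable test.** A reader might infer that it does, but the numbers do not bear this out. A 4 v 8 split has one observed cell in four below five and so goes to chi-squared, yet the smallest expected count is 12 / 2 = 6, where the usual criterion also keeps chi-squared.

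**The variables may not fit the example.** Religion, ethnicity and marital status may have more than two categories, and the simulated larger tables showed no inflation. The article does not give their distributions, so rare categories are an assumption.

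**The effect on the trial's conclusion is nil.** A reader might infer that false imbalances would prompt unplanned adjustment or disturb the main result. The article does not support this. The Abstract already has the GLMM controlling for 14 potential confounders, and nothing makes their choice depend on baseline p-values.

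**Conclusion.** The rule is wrong as written in its type of count and, on its plain meaning, in its direction. The consequence is limited. For some sparse 2x2 baseline tables, an uncorrected chi-squared test at an assumed 5% level gives false imbalances in 12.3%, 6.1% or 6.7% of allocations (4, 5 or 8 women in total with the characteristic, 191 per arm). At the other totals up to 9 the rate is below 5%, and with a continuity correction there is no inflation at any of them. The first specific objective is affected; the GLMM estimate of effectiveness is not. This is a minor point.

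**What to change.** Replace the sentence with: *Fisher's exact test will be used where more than 20% of cells have expected counts below five; chi-squared otherwise.* It would also help to say whether chi-squared for 2x2 tables carries a continuity correction, since the size of the problem depends on it.

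The cost is one sentence, with no change to data collection, participants or the main analysis. Whether to report baseline p-values at all is a separate matter of preference that this correction does not depend on.
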